# Introduction

## 1.1 Background

Regarding occupational rehabilitation, a balance between workload and individual’s work capacity is required for returning to work successfully after an injury or illness. Therefore, it is of great value to evaluate a wide range of physical work requirements and to assess employee’s work capacity across occupational categories. Although several approaches have been made in this regard, there are few objective data available so far and no established thresholds exist. One reason could be that objectifying workload and work capacity is methodically challenging because of their multidimensional nature .

Physical activity is defined as any bodily movement produced by skeletal muscles resulting in energy expenditure *.* In classical work physiology, energy expenditure was therefore considered as basis for assessing the amount of workload *.* However, the energy cost of physical activity may not necessarily be equivalent to body movement . For that reason, modern concepts include also other aspects reflecting the severity of manual work. The ‘Dictionary of Occupational Titles’ (DOT), developed by the U.S. government, classifies professions into five categories (sedentary, light, medium, heavy, very heavy) based on the amount of energy expended as well as on the intensity and duration of lifting or carrying during work . Though, the DOT classification has not been based on quantitative work-related analyses, but rather on consensus meetings of experts. Furthermore, its validity has not been established.

Work capacity can be assessed using functional capacity evaluations (FCEs), which measure the ability of subjects to perform specific activities . Worldwide, there are various FCE protocols available being job specific , pathology specific or of a more general type. Soer et al. applied an evaluation system consisting of 12 work-related tests to establish functional capacity in healthy employees . The assessment included various lifting and energetic exercises as well as coordination tasks. From the test results, normative FCE values were acquired for each DOT-category, which can be compared to patient data in order to make work recommendations.

However, since validity of the DOT has not been proved, further analysis concerning workload assessment is required. Moreover, the application of such complex FCE tools is related to high expenses and efforts and may therefore not be appropriate in a general clinical or field context. Especially in large populations, implementing highly accurate instruments is difficult due to high costs and poor practicability .

For these reasons, the present study will focus on workload, rather than work capacity, by investigating a wide range of physical work requirements across occupational categories. Since physical activity is characterized by various dimensions, such as duration and intensity , these factors will be considered for a comprehensive analysis. However, not only absolute values, but also the distribution of activity pattern may play a role in this context and will therefore be evaluated.

## 1.2 Specific aims

The primary aim of this study is to investigate healthy employees in Switzerland regarding active energy expenditure, physical activity duration at different intensities and the distribution of medium- and high-intensity activity periods of more than ten minutes during a normal working day with focus on differences between occupational categories. Furthermore, the association between physical activity and exercise capacity will be examined.

## 1.3 Hypotheses

### Individuals practising heavy work are more physically active and consume more energy than those with light work.

- - 1. Exercise capacity (VO2max) correlates positively with work and non-work related physical activity.

### 1.3.3 Better trained subjects (with a higher aerobic capacity) show longer periods of medium- and high-intensity activity than untrained individuals.

## 1.4 Potential significance

This study is expected to provide detailed information about physical work requirements and performance criteria of different job categories. This may be valuable regarding treatment and professional reintegration after an injury or illness, since up to now no established thresholds exist. Objective workload data might improve clinicians’ recommendations for a successful return to work.

# Methods

## 2.1 Study design

### 2.1.1 Primary and secondary outcomes

## Our primary objective is to analyze work related physical activity parameters measured by the SenseWear Mini armband across occupational categories. Furthermore, exercise capacity, perceived work intensity, activity behaviour in recreation, quality of life, body composition and several personal and job factors will be investigated as secondary outcomes.

### 2.1.2 Study procedures

In this cross-sectional study, we plan to recruit healthy full-time employed adults from different occupational fields in the area of Basel, Switzerland. It is intended to start with a pilot study in January 2013, in which a total of 15 persons will be examined.

Recruitment will initiate in April 2013 and will end as soon as 300 individuals are included in the study (at the latest in March 2014).

Potential subjects will be contacted and asked for study participation by phone or by mail. Willing individuals meeting the inclusion criteria will fill out the informed consent form before starting the measurement procedure.

At the first study visit, body measurements will be carried out such as height, weight and waist circumference (WC) and body mass index (BMI) will be calculated. In addition, a variety of personal and job related factors will be recorded. Furthermore, subjects will perform a 20 meter shuttle run in order to measure exercise capacity.

During the subsequent week, participants will be instructed to document their daily work activities and to rate their work related physical exertion twice per day using the Borg Scale. Moreover, by wearing the SenseWear Mini armband on seven consecutive days, physical activity and energy expenditure will be objectified.

One week later at the second study visit, all subjects will complete several self-administered questionnaires concerning work and non-work related physical activity behaviour (IPAQ), health-related quality of life (SF-36) and self-assessment of professional activity and its intensity (VAS). In addition, open questions will be asked to each participant about past-week physical exertion in comparison to a normal week.

The time required for the two study visits taking place at the individual’s workstation, will be around 90 minutes per person. In addition, every participant will wear the activity monitor on seven consecutive days.

Termination criteria for the measurements are skin irritations caused by the SenseWear Mini armband and exertional dyspnea during 20 meter shuttle run.

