## 2.2 Selection of study participants

### 2.2.1 Recruitment

In this study, it is intended to recruit 300 subjects from different occupational groups with low, middle and high occupational activity, which are defined in a later section (see chapter 2.3.2). Based on this classification, companies will be selected. In each occupational group, 100 participants will be enrolled. Furthermore, homogeneity of age and gender within each group will be aimed at recruiting.

First, we will contact the management of potential enterprises in order to present our project. If they are interested in collaboration, we will ask for a list of employees, who will then be addressed by a member of our research team. In a further step, individuals will be informed and asked for study participation by phone or by mail. Furthermore, it is planned to distribute study flyers in the companies, so that interested employees have the opportunity to contact us directly. In both situations, the recruitment and information process will be done externally. Thus, negative impact of the employer can be avoided and the selection of study participants will occur randomly. However, the employer’s agreement is essential for the conduction of the study.

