### 2.3.2 Classification of occupations

The reported professions will be classified into 9 categories based on the International Standard Classification of Occupations ISCO-88  *(1. Managers and administrators, 2. Professionals, 3. Technicians and associate professionals, 4. Clerks, 5. Service workers, 6. Agricultural and fishery workers, 7. Construction and related workers, 8. Plant and machine operators, 9. Elementary workers)*. These 9 categories will then be collapsed into 3 groups with low, middle and high occupational activity according to Suva experts in the field of ergonomics (*1st group*: Categories 1 (Managers and administrators) and 2 (Professionals); *2nd group*: Categories 3 (Technicians and associate professionals), 4 (Clerks) and 5 (Service workers); *3rd group*: Categories 6 (Agricultural and fishery workers), 7 (Construction and related workers), 8 (Plant and machine operators) and 9 (Elementary workers). Reliability of this stratification has been previously shown .

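### Nothing keeps the three occupational groups from being measured in different seasons, although the high-activity group includes agricultural and construction workers

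*Protocol*

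**What the plan says.** Four features of the protocol combine here.

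- **Window.** Section 2.1.2: "Recruitment will initiate in April 2013 and will end as soon as 300 individuals are included in the study", and "at the latest in March 2014". Coverage may be four quarters or fewer.
- **One week per person.** The same section: "by wearing the SenseWear Mini armband on seven consecutive days, physical activity and energy expenditure will be objectified". No measurement is repeated in another season.
- **Recruitment by class.** Section 2.2.1: "Based on this classification, companies will be selected. In each occupational group, 100 participants will be enrolled". Age and gender are the only characteristics it aims to keep homogeneous; calendar time is not mentioned.
- **Make-up of the high group.** Section 2.3.2 lists "Categories 6 (Agricultural and fishery workers), 7 (Construction and related workers", followed by plant and machine operators (8) and elementary workers (9).

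Section 2.6.3 makes covariates optional and draws them from the personal and job factors. The list of those factors in 2.3.1 has no measurement date. The aim in 1.2 is to describe activity "during a normal working day with focus on differences between occupational categories".

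**The concern.** Work in agriculture and construction can reasonably be expected to vary with season and weather. If the high group were measured mostly in warm months and another group mostly in cold months, the contrast between them would contain a seasonal component as well as an occupational one. Each person contributes a single week, so no within-person comparison can separate the two, and enrolling more people does not shrink the bias. Section 1.4 wants workload data to inform return-to-work advice where no thresholds exist, so the size of the group difference matters as well as its significance.

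An analysis plan that is not shown could add a season term. It could not restore overlap between groups that was lost at recruitment, so the timing rule belongs in the protocol.

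**Working it through.** **Inputs from section 2.6.4:** 100 per group, SD 730 kcal, expected difference 500 kcal, two-sided 5%.

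**Assumptions (the documents give no value):**
- G: warm-minus-cold gap in outdoor workers, 100–300 kcal per day
- s: outdoor share of the high group, 0.5 or 1
- d: difference between the two compared groups in the share measured in the warm season, 0.5 or 1

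**1. The plan's own figure.** The standard error of a pairwise difference is 730 × √(2/100) = 103.2 kcal. Then 500/103.2 = 4.84, and power is Φ(4.84 − 1.96) = 99.8%. The stated power of more than 90% is met.

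**2. Bias.** If season acts only on outdoor workers in the high group, bias = G × s × d. The reference is the contrast that would be seen had the high group been measured in the same seasonal mix as its comparator. (Against a year-round average, d would be replaced by the high group's own departure from an even mix.)

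| G (kcal) | s = 0.5, d = 0.5 | s = 1, d = 0.5 | s = 1, d = 1 |
|---|---|---|---|
| 100 | 25 (5%; 0.24 SE) | 50 (10%; 0.48 SE) | 100 (20%; 0.97 SE) |
| 200 | 50 (10%; 0.48 SE) | 100 (20%; 0.97 SE) | 200 (40%; 1.94 SE) |
| 300 | 75 (15%; 0.73 SE) | 150 (30%; 1.45 SE) | 300 (60%; 2.91 SE) |

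Percentages are of 500 kcal; SE multiples are bias/103.2.

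**3. Effect on the test.** With no true difference, the rejection rate is Φ(−1.96 + b/103.2) + Φ(−1.96 − b/103.2) for bias b. It is 5.7%, 7.7% and 11.2% at b = 25, 50 and 75, and 16.2% at b = 100. If the bias works against a true 500 kcal difference, power is still 98.5% at b = 75 (425/103.2 = 4.12). It falls to 49% only at b = 300.

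**4. Cost of adjusting.** For a two-level season with warm shares p₁ and p₂ in two groups, r² = [(p₁ − p₂)²/4]/[p̄(1 − p̄)], and the variance is multiplied by 1/(1 − r²).
- 75%/25%: r² = 0.25, factor 1.33, power 98.7%
- 90%/10%: r² = 0.64, factor 2.78, power 82.8%
- 100%/0%: r² = 1, so group and season cannot be separated

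**5. Why an additive season term is not enough.** It imposes one seasonal effect on all groups. Suppose the high group is 90% warm, its comparator 50% warm, and season shifts only the high-group mean, by g. Unadjusted bias is (0.9 − 0.5)g = 0.40g. The pooled season slope is weighted by p(1 − p): 0.09g/(0.09 + 0.25) = 0.26g. The term removes 0.26g × 0.4 = 0.11g and leaves about 0.29g. A group-by-season model with contrasts averaged over seasons avoids this, provided every group has people in every season that is averaged.

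**The case against.** Several stronger readings are tempting, and the documents do not support them.

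- **That the groups are filled one after another, company by company.** A reader might infer this from selecting companies by class. Section 2.2.1 gives no order or timing, and 2.1.2 sets one window for all 300, so parallel recruitment is not excluded.
- **That a bias of 20–60% is to be expected.** That needs every high-group worker to be outdoors and the seasons to be fully separated. The high group also contains machine operators and elementary workers, and no outdoor share is given.
- **That stopping early at 300 confounds the groups.** A shorter shared window limits between-group imbalance. What remains is mainly generalisability: results may describe only the seasons covered.
- **That adjustment for season is ruled out.** Section 2.6.3 permits covariates without closing the list, and an analysis plan may specify more.
- **That the armband itself reads differently by season.** It uses heat flux and skin temperature, but section 2.4.3 gives no evidence of seasonal error and reports validation against doubly labelled water.

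Two further limits stand. The primary endpoints cover working time without commuting or breaks, so the outdoor-work mechanism bears on the two contrasts with the high group and gives no reason to doubt low versus middle. The visual analogue scales and open questions do ask whether the week was normal. That check is partial: a participant may rate a summer week as normal for summer, and the answers do not align the calendar across groups.

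The gap in the scheduling rule survives all of this.

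**Conclusion.** The protocol leaves open a confounding of season with occupational group that sample size cannot remove. It does not create one by rule. Under the assumed gap of 100–300 kcal, the bias in a contrast with the high group is 25–75 kcal with moderate multipliers. It reaches 100–300 kcal (1.0–2.9 standard errors) only at the extreme. Its actual size and direction cannot be found from the documents.

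With pairwise power of 99.8%, detecting high versus low is fairly safe outside that extreme. The estimated size of the workload difference is more exposed. The point is a cheap improvement to make before recruitment starts, not a flaw that invalidates the design.

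**What to change.** **Sections 2.1.2 and 2.2.1.** State that the three groups are recruited concurrently, with roughly equal numbers per group in each calendar quarter as a target. Keep the existing end rule. A hard cap would be unwise: 25 per group per quarter over four quarters gives exactly 3 × 4 × 25 = 300, so a shortfall could not be made up by March 2014, and enrolment depends on employers' agreement.

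**Section 2.6.3.** Derive season from the measurement date and include it as a prespecified covariate in the working-time and recreation models. Add a group-by-season sensitivity analysis with contrasts averaged over seasons. If 300 is reached early, state which seasons the results cover.

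**Cost.** Some scheduling effort and a few degrees of freedom. Calendar quarter takes 3 of the 300 − 3 = 297 residual degrees of freedom, and the interaction takes a further 2 × 3 = 6 in the sensitivity model. Precision is barely affected unless the seasonal imbalance is extreme.

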### 2.1.3 Flowchart

|  | Day **1** | **2** | **3** | **4** | **5** | **6** | **7** | Day **8** |
| --- | --- | --- | --- | --- | --- | --- | --- | --- |
| **Examination** | Body measurements  (Height, weight, WC)  Interview  (Personal and job related factors)  20 meter shuttle run  Instructions for SenseWear Mini Armband | * Wearing period of SenseWear Mini Armband  ° Borg Scale  # Documentation of  work activities |  |  |  |  |  | Questionnaires  (IPAQ, SF-36, VAS,  open questions)  Collection of SenseWear Mini Armband |
| **Location** | At work | * At work and at home  °, # At work |  |  |  |  |  | At work |
| **Time interval** | 60 min | * 7 consecutive days, 23h/day  ° 2x/day (midday, evening)  # 1x/day (evening) |  |  |  |  |  | 30 min |

## 2.2 Selection of study participants

### 2.2.1 Recruitment

In this study, it is intended to recruit 300 subjects from different occupational groups with low, middle and high occupational activity, which are defined in a later section (see chapter 2.3.2). Based on this classification, companies will be selected. In each occupational group, 100 participants will be enrolled. Furthermore, homogeneity of age and gender within each group will be aimed at recruiting.

First, we will contact the management of potential enterprises in order to present our project. If they are interested in collaboration, we will ask for a list of employees, who will then be addressed by a member of our research team. In a further step, individuals will be informed and asked for study participation by phone or by mail. Furthermore, it is planned to distribute study flyers in the companies, so that interested employees have the opportunity to contact us directly. In both situations, the recruitment and information process will be done externally. Thus, negative impact of the employer can be avoided and the selection of study participants will occur randomly. However, the employer’s agreement is essential for the conduction of the study.

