### 2.6.3 Statistical analysis

Statistical analyses will be done using the software R (version 2.15.1) and IBM SPSS Statistics (version 19.0). Statistical significance will be acquired if a p value of less than 0.05 is attained.

Data will be presented by descriptive statistics within occupational groups. Cross tables are reported as counts and percentages. Ordinal variables are reported as median and Interquartile range (IQR). Metric variables are reported as mean and standard deviation (SD).

To evaluate primary endpoints, linear regressions will be performed. Independent variable is “occupational group”, dependent variables are “average daily active energy expenditure”, “average daily physical activity duration” and “average daily number of steps”. Optionally, personal and job related factors can be included in the regression analyses as covariates. If appropriate, data will be log-transformed. Regression results will be presented as differences of means between “occupational categories” with corresponding 95% confidence intervals (C.I.) and p-values. In case of logarithmic distributed data, geometric mean ratios will be presented.

To evaluate secondary endpoints, linear regressions will be conducted. In case of ordinal variables, non-parametric methods will be applied.

Furthermore, the mean and individual time courses of physical activity periods will be plotted for all primary and secondary variables.

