### 2.6.4 Sample-size calculation

Since “average daily active energy expenditure” measured by the SenseWear Mini armband represents a valid and reliable parameter, it is considered to be the most important primary endpoint of the present investigation. For this reason, only this variable is subject to a power calculation. In a previous study, the SD of “average daily active energy expenditure” during a normal work shift was found to be 730 kcal . The expected mean difference between the three occupational groups will be around 500 kcal. Assuming a sample size of 100 subjects in each occupational group, there is a power of >90% to detect a mean difference of 500 kcal between any of these groups. This calculation is based on the assumption of a within group SD of 730 kcal and on a two-sided significance level of 5%.

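### Employees are recruited through companies chosen by occupational group, but the regressions and the power statement make no allowance for company; CIs and p-values are too optimistic if colleagues resemble each other and firms mostly supply one group

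*Protocol*

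**What the plan says.** Section 2.2.1 describes recruitment in two stages. Companies come first: "Based on this classification, companies will be selected. In each occupational group, 100 participants will be enrolled". The study team then approaches employees through the firm: "If they are interested in collaboration, we will ask for a list of employees, who will then be addressed by a member of our research" […]. Flyers inside the firms are a second route. No firm takes part without consent, since "the employer’s agreement is essential for the conduction of the study".

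Section 2.3.2 defines the comparison variable. Each reported profession is coded into one of nine ISCO-88 categories, and these are collapsed into three groups.

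Section 2.6.3 names the primary model: "To evaluate primary endpoints, linear regressions will be performed", with occupational group as the independent variable and personal and job related factors as optional covariates. Differences of means are reported with 95% CIs and p-values. Company is not among the factors listed in 2.3.1.

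Section 2.6.4 gives the power: "Assuming a sample size of 100 subjects in each occupational group, there is a power of >90% to detect a mean difference of 500 kcal", and adds "This calculation is based on the assumption of a within group SD of 730 kcal and on a two-sided significance level of 5"%.

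Nowhere does the protocol mention a number of companies, a number of employees per company, an ICC, a design effect, a random effect or a robust variance.

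**The concern.** Firms are picked because of the occupational group they can supply, so company is the first-stage sampling unit. Most of the contrast between groups is then likely to be a contrast between different sets of firms. The primary endpoints are activity measured during working time, and colleagues at one site share tasks, layout and pace. Some positive correlation within firms is therefore plausible for exactly these outcomes.

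Ordinary regression standard errors ignore such correlation. When the comparison is mainly between firms, the intervals are then too short and the p-values too small for every regression-based primary endpoint (energy expenditure, activity duration, steps). A few untypical firms could pass for an occupational difference. Section 1.4 intends the results to support return-to-work recommendations, so overstated precision matters. The remark in 2.2.1 that participants are selected at random concerns individuals and does not remove variation between firms.

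**Working it through.** **Inputs from the protocol (2.6.4).** n = 100 per group, difference 500 kcal, SD 730 kcal, two-sided 5%.

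**Inputs not in the protocol (assumptions).** Employees per company m, here 10 or 20, so k = 100/m = 10 or 5 firms per group; ICC 0.05 or 0.10; full nesting, meaning each firm supplies one group only. The SD of 730 kcal is taken as the total SD within a group, including variation between firms.

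**Step 1: the stated power.** Standard error of a difference = 730 × √(2/100) = 103.2 kcal. 500/103.2 = 4.84. Power = Φ(4.84 − 1.96) = Φ(2.88) = 99.8%. The claim of over 90% is reproduced, with much to spare, if all subjects are independent.

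**Step 2: how much clustering the power tolerates.** Largest design effect (DE) with 90% power = (500/730)² × (100/2) / (1.960 + 1.282)² = 2.23. With DE = 1 + (m − 1) × ICC, this allows an ICC up to (2.23 − 1)/9 = 0.137 at m = 10 and (2.23 − 1)/19 = 0.065 at m = 20. This is a normal approximation.

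**Step 3: illustration under full nesting.**
- A correct CI is √DE times as wide as the ordinary one.
- Real type I error of the ordinary 5% test = 2 × [1 − Φ(1.96/√DE)].
- Power is given by the normal approximation with 100/DE effective subjects per group, and by a noncentral t with 2(k − 1) degrees of freedom, which allows for the small number of firms.

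| m (firms per group) | ICC | DE | CI width factor | Real type I error | Power, normal | Power, t |
|---|---|---|---|---|---|---|
| 10 (10) | 0.05 | 1.45 | 1.20 | 10% | 98.0% | 96.7% |
| 10 (10) | 0.10 | 1.90 | 1.38 | 16% | 94.0% | 91.3% |
| 20 (5) | 0.05 | 1.95 | 1.40 | 16% | 93.4% | 85.8% |
| 20 (5) | 0.10 | 2.90 | 1.70 | 25% | 81.2% | 70.3% |

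The third row shows that the limit of 2.23 is too generous when firms are few: DE is only 1.95, yet power with company-level degrees of freedom is 85.8%.

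**Step 4: partial nesting.** If firms supply several groups, the inflation is roughly 1 + (m − 1) × ICC × ρ, where ρ is the within-firm correlation of group membership and ρ = 1 is full nesting. With an assumed ρ = 0.5, m = 20 and ICC 0.10 give 1 + 19 × 0.10 × 0.5 = 1.95 instead of 2.90, and a type I error of about 16% instead of 25%. If every firm supplied all groups equally, ordinary regression would be conservative.

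**The case against.** The strongest objection is that occupational group belongs to the person, not the firm. Under 2.3.2 a manager, a clerk and a construction worker in one firm fall into three different groups, and 2.2.1 does not say that each firm supplies only one. A reader might infer that group is in effect a company attribute and that the full inflation 1 + (m − 1) × ICC applies. The protocol does not support that: full nesting is the worst case and an assumption alongside m and ICC. This part stands. Choosing firms by the classification still makes substantial nesting likely.

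A second objection is that power has ample slack. An observed difference of exactly 500 kcal would give 4.84/√2.90 = 2.84 even at the largest design effect shown, above the 5% cut-off of 2.31 on 8 degrees of freedom. That also stands, and nothing in the protocol points to few, large firm samples. It answers the power question only in part, and it does not answer the interval question: slack in power does not correct a CI that is too short.

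A third objection is that 2.6.3 names no variance estimator, so an SAP could adopt cluster-robust standard errors without contradicting it. That is fair for the analysis. It does not cover 2.6.4, where the power basis is fixed as 100 subjects per group with no allowance for company, nor the spread of recruitment over firms, which no analysis can repair afterwards.

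**Conclusion.** The concern holds in conditional form. The protocol recruits through companies and takes no account of company in its stated model or its power. If the within-company correlation is positive and firms mostly supply one group, the CIs and p-values for the group differences are too optimistic. In the illustration the intervals should be 1.20 to 1.70 times as wide and the real type I error is about 10 to 25%. These figures rest on assumed m, assumed ICC and full nesting; the protocol gives none of the three, and the effect is smaller with mixed firms.

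A reader might also infer that the stated power is wrong or below 90%. It is not shown to be: 99.8% follows from the protocol's own inputs under independence, and over 90% survives with many small company samples. The figure depends on the number of firms, which is not stated. Validity of the intervals is the more important part of the point.

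**What to change.** - **Data.** Record a company code for each participant. The firm is known from recruitment, so this costs almost nothing.
- **Section 2.6.3.** Fit the group comparisons with a random intercept for company, or keep linear regression with cluster-robust standard errors, in either case with a small-sample correction. Company as a fixed covariate is not a substitute, because under heavy nesting it would absorb most of the group contrast.
- **Section 2.6.4.** Keep the figure under independence, and add power over a stated range of ICC and employees per company, with the expected number of firms per group.
- **Recruitment.** Spreading enrolment over more firms is desirable where feasible, but a fixed cap is not required. Ten firms per group would mean about 30 consenting employers if each supplies one group, within the window from April 2013 to March 2014 (2.1.2). That is a real burden, and any specific cap would rest on an assumed ICC.

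The downside is somewhat wider CIs and a slightly less favourable stated power.

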## 2.5 Data collection, management and retention

A member of the study team will contact employees from selected companies around Basel. Participation is voluntary and can be revoked at any time. There is no disadvantage for individuals that do not take part in the study.

To ensure a standardized process, measurements will be carried out always by the same study nurses trained for this purpose. For data collection and management, data will be anonymized and participants will be identified by a study number. Test results will be transmitted to the participants after all investigations have been performed.

All study related records and informed consent documents will be retained in the Clinic of Internal Medicine at the University Hospital of Basel as long as required by the applicable Swiss regulatory requirements (10 Years). Moreover, monitoring visits, audits and regulatory inspections will be granted direct access to the obtained data.

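### The protocol calls participant selection random, but the recruitment it describes yields volunteers from consenting companies, with no record of route or non-response

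*Protocol*

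**What the plan says.** Protocol section 2.2.1 (Recruitment) concludes that "the selection of study participants will occur randomly". The reason it gives is that recruitment and information are handled externally, which is also meant to keep the employer from exerting a negative influence.

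The same section describes these steps:

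- Companies: "Based on this classification, companies will be selected".
- Entry of a company: "If they are interested in collaboration, we will ask for a list of employees". The section adds that "the employer’s agreement is essential for the conduction of the study".
- Employees on the list: "individuals will be informed and asked for study participation by phone or by mail".
- Other employees: "it is planned to distribute study flyers in the companies, so that interested employees have the opportunity to contact us directly".
- Targets: 100 participants per occupational group, with homogeneity of age and gender sought within each group.

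Section 2.1.2 lets willing, eligible people enter after consent. It ends recruitment at 300 participants, or in March 2014 at the latest. Section 2.5 says "Participation is voluntary and can be revoked at any time".

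**The concern.** A random sample is one in which a chance mechanism with known properties decides who is approached. Section 2.2.1 names no such mechanism and offers external handling in its place. A reader of the protocol, or of a paper that repeats the sentence, would credit the sample with a property that the described procedure does not give it.

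This matters because section 1.4 presents the study as a source of workload information by job category, for use in return-to-work advice. Reference data of that kind depend on who was sampled. The occupational groups are also broad: section 2.3.2 places technicians, clerks and service workers in one group, and four ISCO categories in another. Without a sampling rule, the mix of jobs within a group depends on which companies agree and who comes forward. A study with a maximal run and a week of monitoring may also appeal more to fitter employees.

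The protocol makes no provision to record whether a participant came from a list or a flyer, or how many were invited and did not respond. If this is not recorded during recruitment, it cannot be reliably reconstructed afterwards.

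**Working it through.** **Step 1: the claim against each stage described.**

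| Stage | What the protocol describes | Chance mechanism stated? |
| --- | --- | --- |
| Choice of company (2.2.1) | By occupational classification | No |
| Entry of company (2.2.1) | Management interest and employer agreement | No |
| Approach from employee list (2.2.1) | Phone or mail; no draw, fraction or order given | No |
| Flyer (2.2.1) | Employee makes contact | No; self-referral |
| Enrolment (2.1.2, 2.5) | Willing individuals; voluntary | No |

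The only support for the word is external handling, which concerns who does the recruiting and not how people are picked. The flyer route cannot be random under any reading. The list route could be made random, but nothing in the text says that it will be.

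**Step 2: the plan's own figure.** Section 2.6.4 gives n = 100 per group, SD = 730 kcal, a difference of 500 kcal and a two-sided 5% level, and states power above 90%.

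- SE of a pairwise difference = SD × √(2/n) = 730 × √(2/100) = 103.2 kcal.
- 500 / 103.2 = 4.84 standard errors.
- Power = Φ(4.84 − 1.96) = Φ(2.88) = 0.998.

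The stated power is confirmed. It allows for sampling error only and says nothing about selection.

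**Step 3: how sensitive a contrast would be.** The protocol contains no figure from which a selection bias could be estimated. The shift b below is therefore an assumption, shown as a range.

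- Coverage of the nominal 95% interval = Φ(1.96 − b/SE) − Φ(−1.96 − b/SE).
- False-positive rate with no true difference = 1 − coverage.
- Power when b reduces a true 500 kcal difference = Φ((500 − b)/SE − 1.96).

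| Assumed shift b (kcal) | b / SD | Coverage | False-positive rate | Power |
| --- | --- | --- | --- | --- |
| 0 | 0 | 95% | 5% | 99.8% |
| 50 | 0.07 | 92% | 8% | 99% |
| 100 | 0.14 | 84% | 16% | 97% |
| 150 | 0.21 | 69% | 31% | 92% |
| 200 | 0.27 | 51% | 49% | 83% |
| 250 | 0.34 | 32% | 68% | 68% |

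If the true difference is near 500 kcal, a modest shift is unlikely to reverse the sign of the comparison. The interval estimates promised in section 2.6.3 are more exposed. A larger sample would not remove such a shift.

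**The case against.** The best defence is context. The sentence follows from the wish to avoid employer influence, so the word may mean no more than that the employer does not hand-pick participants. No analysis in sections 2.6.3 or 2.6.4 uses sampling weights or sampling fractions. Volunteering is unavoidable in any study that requires consent. All of this stands, but it explains the word without making it correct.

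Several stronger readings are tempting, and the protocol does not support them:

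- A reader might infer that no random draw will be made. The text is silent on whether all listed employees are approached and in what order; a draw is not described.
- A reader might infer that recruitment runs unchecked until 300 people are in. There is also a target of 100 per group, an aim for age and gender within groups, and a calendar limit.
- A reader might infer that the traits behind volunteering go unmeasured. Participants have predicted VO2max (2.4.2), IPAQ scores and armband data in recreation (2.6.2), and personal and job factors (2.3.1). SF-36 is collected for confounder adjustment (2.3.4). What the protocol does not provide for is a record of route and of non-responders. Covariates in the regressions are optional (2.6.3), and they describe participants only.
- A reader might infer that the group contrasts are biased. The primary endpoints cover working time only (2.6, 2.6.1), which job tasks may drive more than a liking for fitness studies. Flyers are not restricted to any one group.
- A reader might attach a size. Suppose flyer recruits were 0.2 to 0.4 SD more active and made up half of one group and none of another. The shift would be 0.5 × 0.2 × 730 = 73 kcal to 0.5 × 0.4 × 730 = 146 kcal, or 15% to 29% of 500 kcal. None of those inputs comes from the protocol, and the split is extreme, so this is not evidence of how serious the problem is.

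**Conclusion.** The statement in section 2.2.1 is wrong as written. On the procedure described, the sample consists of volunteers from consenting companies, and the protocol provides for no record of recruitment route or non-response. The consequence that can be asserted firmly is a limit on the representativeness of the job-category workload data, which are the study's stated purpose.

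Bias that differs between occupational groups is plausible but not shown, and its size cannot be derived from the protocol. The coverage figures (92% down to 32% for shifts of 50 to 250 kcal) rest on assumed shifts together with the planned SD and group size. They show what a shift would do and do not indicate that one is present. The point should be corrected before recruitment, but it does not undermine the direction of a primary comparison if the true difference is near the planned 500 kcal.

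**What to change.** 1. Delete the claim of random selection in section 2.2.1 and describe a volunteer sample from consenting companies.
2. Invite employees from the lists already requested in random order, within the age and sex targets, up to 100 per occupational group.
3. Record each participant's route (list or flyer), and the numbers invited and responding per company and per group.
4. Repeat the primary contrasts without flyer recruits as a sensitivity analysis.
5. State company self-selection and non-response as limitations, since random invitation removes neither.

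Flyers can stay. Whether to treat them as a main or a back-up route is a design preference on which this point does not depend.

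The cost is a change of wording, a random ordering of lists, one extra variable and a set of counts, with slight extra administration and possibly slightly slower enrolment. Items 2 and 3 have to be in place before recruitment starts.
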